## Study Procedures

### Suicidal Ideation and Behavior

Does this research qualify as a clinical investigation that will utilize a test article (ie- drug or biological) which may carry a potential for central nervous system (CNS) effect(s)?

No

### Procedures

This 4-arm RCT will compare the relative effectiveness and cost-effectiveness of process versus outcome-based financial incentives in improving LDL cholesterol in patients who are at high risk for CVD and have been prescribed statins. Adherence in all groups will be measured using an electronic pill container as a recording device. The intervention will consist of an active phase of 12 months followed by 6 additional months of observation. Participants will be randomized evenly into one of 4 arms - process, outcomes, combination process plus outcomes, usual care (see figure for arm descriptions). All potentially eligible employees within the CVS-covered group will be contacted via existing communication channels through CVS. Potentially eligible employees will have evidence of diabetes medication use and/or CVD medication use in the CVS pharmacy database. These individuals will be sent letters (paper or email) describing the study and inviting them to enroll. Potentially eligible patients recruited from Penns Health system/LGH will be contacted by the study team via letter, email and phone calls. Interested participants will sign up online or by phone with a study coordinator based at UPENN and will be asked to provide informed consent. These individuals will have the option of entering data related to eligibility and their demographic and clinical characteristics through the Way to Health internet portal or by phone. Each potential participant will visit a local participating laboratory (through the Quest national chain of commercial laboratories or their doctor if they are from Penn Medicine/LGH) to confirm that their LDL is 100 mg/dl. The Quest corporation has 24 hour appointment scheduling and 2,000 lab locations; these locations are in every state as well as Puerto Rico. The enrollment interview and baseline labs will allow investigators to determine final eligibility for the study. Our group has agreements in place with the Quest chain allowing research participants nationwide to have phlebotomy (blood draws). In the context of generous participation incentives (as will be provided in this study), the requirement of providing biological specimens at local laboratories has not been a barrier to program implementation. In another ongoing study, we have used Quest to enable 500 participants to get labs drawn at local laboratories. Randomization will be performed through the Way to Health platform. Randomization will be stratified by employer (should more than one employer be involved to recruit a sufficient number of participants) and will use block randomization with variable block sizes. After reviewing the intake data and LDL, research staff will notify each participant of assignment using their preferred means of communication. All participants will receive an electronic pill container through the mail and will receive careful instructions about study procedures for their assigned arm. Throughout the study, coordinators will remain available to answer questions about devices use and other study procedures. LDL Measurement Schedule. Participants will have six LDL laboratory checks, at months 0, 3, 6, 9, 12 and 18 months. To maximize the likelihood that these LDL measurements are completed, the Way to Health participant tracking system will remind the study coordinators when each participant is due to visit a lab. We will obtain extensive contact information including preferred mode of communication - from each participant and update it at each follow-up visit. Participants who miss scheduled LDL checks will receive four reminders. Patients will receive \$50 after enrollment, initial blood work, and setting up the device. A subset of participants will receive \$100 after enrollment to test whether higher participation incentives increase recruitment rate. Participants will receive \$50 for each subsequent lab check and \$75 for the 12 month LDL check (the primary outcome). Administration of Process Incentives for Daily Adherence. The process financial incentive involves a daily sweepstakes for taking the statin medication. The sweepstakes has two components a high probability/low value reward as well as a low probability/high value reward. We will assign each participant in the Process (arm 1) and Process plus Outcome (arm 3) a two-digit number. Each day, the electronic pill container will automatically upload the previous days data about each participants statin adherence via a wireless internet connection to the Way to Health database at UPENN. We will let each participant pick a two-digit sweepstakes number. Each day, Way to Health software will compare this number with a random two-digit number generated by Way to

Health to determine eligibility for sweepstakes awards. For a participant who was adherent the previous day, if the two digit number matches exactly (probability of 1 in 100), the participant will win \$50. When the two-digit number does not match, but either the first digit or second digit matches, the subject will win \$5 (probability of 18 in 100). The expected value of this sweepstakes is \$1.40/day such that total winnings over the 12-month trial for a participant with perfect adherence will have an average expected value of \$511. An important feature of the sweepstakes is that each eligible participant will receive daily messages about the amount they won. Non-adherent participants will also receive daily feedback about whether they would have won if they had been adherent. This program incorporates key aspects of optimal design, including objective and reliable confirmation of behavior change at frequent intervals, large potential payments to reinforce the target behavior, frequent reinforcement using high probability/low value awards, and the use of anticipated regret, a powerful motivator. We set the expected value of the sweepstakes at \$1.40/day based on our previous success in significantly affecting weight loss and medication adherence with this design. In addition, there is evidence that a patient with established CVD has health expenditures ranging from \$4,500 to as high as \$30,000 per year, suggesting that \$1.40/day incentives if effective, could be cost-effective due to the potential savings in avoiding future CVD events.

**Administration of Outcome Incentives for LDL.** Participants in the outcomes arms (arms #2 and #3) will receive payments if their LDL decreases at least 10 mg/dl in the 3 months since the last visit. Over a year, these payments will be equivalent in magnitude to those in the process arm. The 3-month payment for the Outcome arm (arm #2) will be \$126, while the payment for the Process with Outcomes Incentive arm (arm #3) will be half this value, or \$63. Notably, if a participant in the Outcomes arm or the Process plus Outcomes arm achieves a reduction in LDL 20 mg/dl during one quarter of the trial and that reduction persists during the next quarter, the participant would be eligible for the outcome incentive at the end of both quarters, even if no further reduction in LDL took place during the second quarter. For instance, if a patient in the Outcome arm had an LDL decrease from 150 to 130 mg/dl between baseline and month 3, and also had an LDL of 130 mg/dl at month 6, that person would receive the incentive payment at month 3 and month 6. Participants in the intervention arms will be informed if they fail to meet adherence or LDL goals, and thereby are not eligible for payments. Providing this feedback may also improve adherence by taking advantage of anticipated regret.

**Outcomes. LDL cholesterol.** The primary outcome will be change in LDL cholesterol between baseline (study enrollment) and 12 months. We will also measure LDL cholesterol at 18 months three months after interventions have ended. The 18 month measurement will allow us to ascertain the durability of lipid-lowering effects attributable to financial incentives. LDL cholesterol is a strong risk factor for CVD, and reductions in LDL for instance, through statin treatment lead to meaningful reductions in the risk of cardiovascular events. LDL cholesterol is easily assessed through a blood test. LDL can be calculated indirectly from other measured lipids if the patient is fasting, or measured directly. We will measure LDL directly. Statin adherence assessed through Vitality GlowCaps, MedSignals, Adheretech, or Wisepill (secondary outcome). The electronic pill container provides continuous data about bottle opening and a valid approach to verifying self-administered pill taking, reflecting not only daily use but also patterns of drug use and timing. This method of adherence measurement assumes that each time the device is opened, a statin dose is taken, and that statin doses are not taken when the cap is not opened. The electronic pill containers function just like regular pill bottles. Numerous studies have established the validity of electronic pill container measures, such as those provided by GlowCaps. Other methods have been developed to assess medication adherence, such as patient self-report, pill counts, and medication possession ratio, but there is no method that is widely recognized as superior to electronic pill containers. Although it is possible for patients to open a pill bottle but not take their statin, evidence suggests that once an individual opens a pill bottle, it is uncommon for an individual not to take the pill. However, to address this limitation of electronic pill bottles, some investigators of medication adherence have advocated for supplementing adherence data using electronic pill containers with another method of adherence assessment such as pill counts or medication refill data. In our study, we have adopted this approach of also measuring statin adherence with pharmacy refill data. Our group has extensive experience running clinical trials in which participants use GlowCaps. We encourage participants to use the electronic pill container for study medications while continuing the usage of existing pill-organization methods such as pillboxes for other pills. Statin adherence assessed through the Medication Possession Ratio (MPR, secondary outcome). Because participants may have pharmacy benefits through CVS-Caremark, we will also have data about when patients filled statin prescriptions and number of statin pills that the patients received. The MPR is calculated as the number of days for which a medication is supplied (numerator, consisting of number of statin pills provided by CVS to the participant) over a specified interval of time (denominator, for this study 365 days the duration of the interventions). The MPR will provide a secondary means to compare statin adherence across each arm. Limitations to the MPR data include 1) the problem that patients may

receive the statin medication but not take the pills, which could lead to overestimation of adherence; and 2) the problem that when prescribing doctors lower the statin dose, patients may continue to use existing pills (e.g. cutting a 40mg tablet into 20 mg half-tablets and taking the half-tablets) and refill the medication at a longer interval, leading to underestimation of adherence. However, the MPR offers complementary information about adherence and will be analyzed both during the 12 months of the intervention and for an additional 6 months post-intervention. Adherence to non-statin medications assessed through the Medication Possession Ratio (secondary outcome). It is unknown whether financial incentives for statins and LDL cholesterol may lead to positive or negative spill-over effects for other medications. For instance, a focus on taking statins could lead participants to neglect the need to take their other medications. On the other hand, by helping participants reinforce good adherence habits for statins, participants might be more likely to take other medications as well. Comparisons of the MPR for non-statin medications across treatment arms will inferences about the spill-over effects of process vs. outcomes-based financial incentives. We will specifically examine spill-over effects related to other medications commonly used to lower CVD risk, e.g. blood pressure medications. Potential confounders and mediators. Randomization should balance measured and unmeasured confounders across study arms. However, we will measure potential confounders during study enrollment and compare their distributions across arms and perform adjustments if necessary. We will have data on participant demographics, self-reported socioeconomic status, co-morbidities, baseline MPR for statins and other medications, and baseline LDL cholesterol. Notably, these variables may also serve as either effect-modifiers (predicting the magnitude of an interventions effect across participant groups) or mediators (variables related to mechanisms whereby the intervention works) in the intervention-outcome pathway. For variables believed to be mediators, we would not make adjustments (see Data Analysis Plan, § IV.E.2.). Participant characteristics. Baseline data will be collected through the Way to Health internet portal and/or through phone interviews with study coordinators. Baseline data will be comprised of self-reported demographics (e.g., age, sex, race/ethnicity, income, education, marital status, employment, health insurance) and co-morbidities and medication adherence questions. Participant Characteristics. At the 6, 12 and 18 month interviews, participants will complete a medication adherence questionnaire. During the 12-month interviews, we will also collect data from participants about time spent using the study device, getting labs drawn, and interacting with the Way to Health interface; these time estimates will be used for cost-effectiveness analyses.

**The following documents are currently attached to this item:**

*There are no documents attached for this item.*

### **Deception**

Does your project use deception?

No

### **International Research**

Are you conducting research outside of the United States?

No

### **Analysis Plan**

Data analysis plans. We will explore and describe participant attributes across the 4 arms using graphical approaches and summary statistics (means, medians, standard deviations and the interquartile range). The primary analysis will be intent-to-treat using a linear regression analysis of the effect of treatment assignment on the outcome of change in LDL from baseline to 12 months. The model will be stratified by center and baseline will also be added as a covariate in order to improve efficiency of the analysis. Secondary analyses will adjust for measures of socioeconomic status (SES) and educational attainment (EA). We will explore whether SES and EA act as effect modifiers. We will assess model fit using standard linear regression diagnostics. In additional exploratory analyses, longitudinal models will examine the series of LDL values over time, to determine the shape of the trajectory and consider whether those trajectories differ by treatment group. All hypothesis tests will be two-sided. As a secondary analysis, we will compare the effect of the interventions vs. control among the subgroup of patients who are African-American and/or Hispanic. To maximize the power for this exploratory analysis, we will pool participants in all three incentive arms and compare to control participants. Missing data: Given low rates of drop-out in our other financial incentive studies and because this trial is low-risk, we anticipate low rates of drop-out. As with our other studies, we are diligent in proactively encouraging complete follow-up. Generous participation incentives, as well as multiple reminders

generated by the Way to Health infrastructure, will encourage participants to check their LDL at 3 month intervals. Notably, if participants change employers or benefit-plans, they will continue eligible to remain in the study. Given the rarity of serious side effects and the fact that participants have LDL levels greater than the optimal range for patients with diabetes or CVD, it is unlikely that prescribing physicians will terminate statin treatment. We will monitor completion rates closely during the study. If rates of missing data exceed 15% we will implement approaches aimed at increasing compliance with the protocol. Prior to commencing our analyses, we will compare drop-out and missing data across the 4 arms and will examine associations between participant characteristics and missing data rates. In secondary analyses, we will implement sensitivity analyses to investigate the maximum effect that missing data could have on our results and inferences.

**Sensitivity Analyses, Device Failure:** While the primary analysis is intent to treat, we will characterize our subjects in a number of ways to explore possible impacts of the period with higher rates of device failure. Our study is not powered for hypothesis tests of these effects, and thus the analysis will be exploratory. The following analyses will be conducted:

1. We will stratify the primary analysis by whether a subject experienced two or more weeks of time in the window of time when the devices failed at rates higher than previous studies. Estimates and 95% CI of the effect sizes for the two strata will be determined with the goal of determining whether is evidence of a reduction in effect size due to an excess of faulty devices.
2. For each subject we will create a variable quantifying the proportion of their treatment time in the window with properly functioning devices. For most subjects, this variable will be 1, but for a subjects with say 2 months in the window of faulty devices, this would be  $61/356=.83$ . We will additionally include a variable indicating whether a subject required a device swap. These variables will be included in the primary regression model. Of interest is whether the LDL levels at 12 months (change from baseline) are associated with either variable, and whether the association between LDL level at 12 months and treatment group is confounded by either variable. Additionally, we anticipate that any effect of device malfunction should primary affect the response of subjects on the Process or the Process & Outcome arms. We will thus repeat our analyses separately with these two arms.
3. We will use a logistic regression to determine whether the likelihood of completing the study (lab visit at 12 months) is associated with the proportion of time with a properly functioning device, or the occurrence of a device swap.
4. We will explore patterns of adherence over time as a function of device type. Unfortunately having a faulty device means that we do not have reliable adherence data during the period of device failure. Thus questions will be explored using regression models with data from the periods when the devices were functioning normally. These include:
  - a. Do mean rates of compliance differ by device for subjects randomized to a single device for the entire study period. Does the decline over time in compliance differ by device for subjects randomized to a single device over the study period.
  - b. On average, during the period when our devices returned to normal functioning, are compliance rates similar for subjects who were exposed to faulty devices versus subjects who had normally functioning devices. These will be GEE models with a binary outcome for each day (compliant or not). The predictors include time on study, an indicator variable of whether the subject was on study during the period when the devices failed (or a quantitative variable indicating proportion of time with a functioning device), and an indicator variable for whether subjects experienced more than one device. The analysis will be carried out for the study as a whole (including a treatment indicator), and for each treatment group.

**Cost effectiveness analysis.** Measurement of costs and cost effectiveness. For our initial analysis, we will take a payer perspective. We will complete a within-trial analysis comparing incremental costs and incremental change in LDL in each arm, compared with control, during the 12 months of the trial. As a secondary analysis, we will substitute a societal perspective, which will include costs to patients, such as transportation and the time the patient devotes to the intervention. For both these analyses, costs will include: (1) incentive payments to participants (excluding incentives specific to the research); (2) costs of lab tests for those interventions in which lab tests are necessary to decide whether the participant has earned an incentive payment; (3) operational costs of implementing the interventions, including staff time administering the incentives and the computer platform to deliver the incentives (the Way to Health platform used in this study or an alternative that might be used by an employer); and (4) costs of the adherence measurement device (the electronic pill bottle and fees for connecting to the computer platform). We will also include the drug costs associated with statin medication use when adherence improves. Following usual practice in cost-effectiveness analysis we will conduct sensitivity analyses to assess the impact of uncertainty about these data, e.g., the standard error of the estimate of effectiveness, and to explore variations that might occur across employers. For the societal perspective cost-effectiveness analysis, we will follow the recommendations of the Second Panel on Cost-Effectiveness in Health and Medicine to compute additional costs to patients related to participating in an incentives program, including medication side effects, and time spent on the intervention, including travel and waiting time (using data from American Time Use Survey); time will

be valued at appropriate wage rates. Long-term Effects of LDL Reductions on CVD Events and Cost-Effectiveness: The goal of lowering LDL is to prevent CVD complications. To estimate the cost and effectiveness associated with preventing cardiac outcomes, if our primary analyses of effectiveness indicate significant effects of the intervention, we will use a validated model of long-term cardiac risk, the Coronary Heart Disease (CHD) Policy Model. The CHD Policy Model is a computer-simulation, state-transition (Markov cohort) model of the incidence and prevalence of CVD (myocardial infarction, sudden death, revascularization, angina, stroke) and of the mortality and costs associated with these conditions in U.S. adults. The Model has been used to describe trends in CVD, project the effects of interventions to reduce CVD risk, and model the cost-effectiveness of interventions. [name], who leads the core modeling team, will adapt the Model to our study population, individuals with diabetes and/or known CVD. Based on decreases in LDL observed in the arms of this study, the Model will estimate the number and type of CVD events avoided, the quality-adjusted life years (QALYs) gained, and CVD treatment costs in each arm. We will use these estimates to calculate the cost-effectiveness of the intervention in each arm. Costs and health effects will be discounted 3% per annum. Return on investment: In addition to the cost-effectiveness analysis, if our primary analyses of effectiveness indicate significant effects of the intervention, we will conduct an analysis of potential return on investment for employers, the business case for preventing expensive health complications in the short- to medium-term. Using the CHD Policy Model we will estimate costs and savings of an incentives plan to the employer 3, 5, and 7 years after implementation. Savings will include reduced medical expenditures due to avoided CVD events and complications as well as increases in projected productivity as a result of reductions in CVD disability and death. Cost-effectiveness References 1. Peter J. Neumann, Gillian D. Sanders, Louise B. Russell, Joanna E. Siegel, Theodore G. Ganiats, editors, Cost-Effectiveness in Health and Medicine, second edition, New York: Oxford University Press, 2016. 2. Bibbins-Domingo K, Coxson P, Pletcher MJ, Lightwood J, Goldman L. Adolescent overweight and future adult coronary heart disease. *N Engl J Med* 2007;357:2371-9. 3. Odden MC, Coxson PG, Moran A, Lightwood JM, Goldman L, Bibbins-Domingo K. The impact of the aging population on coronary heart disease in the United States. *Am J Med* 2011;124:827-33 e5. 4. Lazar LD, Pletcher MJ, Coxson PG, Bibbins-Domingo K, Goldman L. Cost-effectiveness of statin therapy for primary prevention in a low-cost statin era. *Circulation* 2011;124:146-53. 5. Pletcher MJ, Lazar L, Bibbins-Domingo K, et al. Comparing impact and cost-effectiveness of primary prevention strategies for lipid-lowering. *Ann Intern Med* 2009;150:243-54. 6. Lightwood J, Bibbins-Domingo K, Coxson P, Wang YC, Williams L, Goldman L. Forecasting the future economic burden of current adolescent overweight: an estimate of the coronary heart disease policy model. *Am J Public Health* 2009;99:2230-7.

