**Administration of Process Incentives for Daily Adherence.** The process financial incentive involves a daily sweepstakes for taking the statin medication. The sweepstakes has two components a high probability/low value reward as well as a low probability/high value reward. We will assign each participant in the Process (arm 1) and Process plus Outcome (arm 3) a two-digit number. Each day, the an electronic pill container will automatically upload the previous days data about each participants statin adherence via a wireless internet connection to the Way to Health database at UPENN. We will let each participant pick a two-digit sweepstakes number. Each day, Way to Health software will compare this number with a random two-digit number generated by Way to Health to determine eligibility for sweepstakes awards. For a participant who was adherent the previous day, if the two digit number matches exactly (probability of 1 in 100), the participant will win \$50. When the two-digit number does not match, but either the first digit or second digit matches, the subject will win \$5 (probability of 18 in 100). The expected value of this sweepstakes is \$1.40/day such that total winnings over the 12-month trial for a participant with perfect adherence will have an average expected value of \$511. An important feature of the sweepstakes is that each eligible participant will receive daily messages about the amount they won. Non-adherent participants will also receive daily feedback about whether they would have won if they had been adherent. This program incorporates key aspects of optimal design, including objective and reliable confirmation of behavior change at frequent intervals, large potential payments to reinforce the target behavior, frequent reinforcement using high probability/low value awards, and the use of anticipated regret, a powerful motivator. We set the expected value of the sweepstakes at \$1.40/day based on our previous success in significantly affecting weight loss and medication adherence with this design. In addition, there is evidence that a patient with established CVD has health expenditures ranging from \$4,500 to as high as \$30,000 per year, suggesting that \$1.40/day incentives if effective, could be cost-effective due to the potential savings in avoiding future CVD events.

**Administration of Outcome Incentives for LDL.** Participants in the outcomes arms (arms #2 and #3) will receive payments if their

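### The secondary societal cost-effectiveness analysis counts incentive payments as a cost without crediting the participants who receive them, so each incentive arm's societal cost is overstated by the amount paid out.

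*Combined protocol and SAP*

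**What the plan says.** The cost-effectiveness plan is in the protocol, Analysis Plan, under Cost effectiveness analysis. The SAP has no section on it.

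- **Order of perspectives.** The payer comes first: "For our initial analysis, we will take a payer perspective". The societal view is secondary: "we will substitute a societal perspective, which will include costs to patients, such as transportation and the time the patient devotes to the intervention".
- **Comparison.** The within-trial analysis is described as "comparing incremental costs and incremental change in LDL in each arm, compared with control, during the 12 months of the trial".
- **Shared cost list.** The list is introduced for the two perspectives together: "For both these analyses, costs will include: (1) incentive payments to participants (excluding incentives specific to the research"). The only payments carved out are those made for research purposes.
- **Delivery costs.** These are a separate item: "operational costs of implementing the interventions, including staff time administering the incentives and the computer platform to deliver the incentives". Laboratory tests needed to decide payment and the adherence device are further items, and statin drug costs are added.
- **Patient side of the societal analysis.** The plan invokes the Second Panel's recommendations "to compute additional costs to patients related to participating in an incentives program, including medication side effects, and time spent on the intervention", with time valued at wage rates. Every patient-side entry is a burden. No receipt appears.

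**The concern.** Item (1) of the list is right for a payer, because the money leaves the payer's account. The societal analysis, as the plan itself defines it, also includes the patient. The same money that leaves the payer arrives with the participant, so across the two parties it nets to zero. The plan records the outlay and omits the receipt.

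The payment cannot be kept as a stand-in for the participant's effort, because that time is already charged separately.

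Aim 4 is the cost-effectiveness of each intervention. Followed as written, the plan would give a societal result in which each incentive arm looks more expensive than it is. The excess would grow with the amount participants earn.

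**Working it through.** **Inputs**

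- Process arm prizes: $50 with probability 0.01 and $5 with probability 0.18 per adherent day (Administration of Process Incentives for Daily Adherence).
- Outcome arm: $126 per quarter. Process plus Outcomes arm: $63 per quarter. There are four quarters (Administration of Outcome Incentives for LDL).
- Process plus Outcomes arm: daily sweepstakes worth $0.70 in expectation. Control: no incentive (both from Design).
- Design difference against control: 10 mg/dl (Accrual, power text).

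**Step 1. Reproduce the plan's figure.** 0.01 × 50 + 0.18 × 5 = 0.50 + 0.90 = $1.40 per day, and 365 × 1.40 = $511. This matches the protocol, where "total winnings over the 12-month trial for a participant with perfect adherence will have an average expected value of" $511.

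**Step 2. Upper bounds in the other arms.** Outcome: 4 × 126 = $504. Process plus Outcomes: 365 × 0.70 + 4 × 63 = 255.50 + 252 = $507.50. Control: $0.

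**Step 3. The accounting.** Let P be the average incentive paid per participant in an arm.

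- Payer and participant together: (+P) + (−P) = 0.
- Plan as written: (+P) + 0 = P.
- Control contributes 0 either way, so incremental societal cost is overstated by P.

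**Step 4. Plausible values of P below the maximum (assumed success rates).**

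- Process: 0.80 × 511 = $408.80; 0.50 × 511 = $255.50.
- Outcome: one, two or three targets met give $126, $252 or $378.
- Process plus Outcomes at 50% adherence and two targets met: 0.50 × 255.50 + 2 × 63 = 127.75 + 126 = $253.75.

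**Step 5. Effect on cost per mg/dl.** The ratio shifts by P divided by the LDL difference from control. Process payments depend on adherence and not on LDL, so they can be set against the design difference: at most 511 / 10 = $51.10 per mg/dl, and 255.50 / 10 = $25.55 at 50% adherence.

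Outcome payments are tied to LDL. Each needs a fall of at least 10 mg/dl since the previous visit, except that a 20 mg/dl fall which holds for the next quarter earns two. All four payments therefore need a within-person fall of about 40 mg/dl (4 × 10 or 2 × 20). If everyone in the arm earned $504, a 10 mg/dl difference would require control to fall by about 40 − 10 = 30 mg/dl, and a 5 mg/dl difference by about 35. The $504 maximum should not be divided by 10 or 5. The outcome part of the $507.50 has the same limit. A coherent illustration is one sustained 10 mg/dl fall in every participant, with no change in control: 126 / 10 = $12.60 per mg/dl.

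**Step 6. Differences between arms.** The maxima differ by at most 511 − 504 = $7. Realised payouts could differ more. If Process ran at 80% adherence and Outcome participants met one target on average, the gap would be 408.80 − 126 = $282.80, all of it transfer.

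**The case against.** **Scope.** The societal analysis is secondary, within the last of four aims. The initial payer analysis counts the payments correctly, as would the employer return-on-investment analysis, and the LDL analysis is untouched. This stands. A reader might infer that Aim 4 as a whole is compromised; the documents do not support that.

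**Easy to undo.** The payments are a discrete item, separate from administration and device. If costs are reported by item, a reader could subtract them. That is so, but the plan does not promise itemised reporting, and the headline societal figure would still be wrong.

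**Second Panel.** The plan cites these recommendations for the societal analysis, and following them might bring in the receipt. In the plan's wording the citation covers additional costs to patients. It does not remove or offset the payment item, which the text applies to both analyses. How the analysts would handle receipts in practice cannot be seen from the documents.

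**Planned sensitivity analyses.** These address uncertainty in the data and variation across employers. They do not address which items belong to which perspective.

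**Ranking of arms.** A reader might infer that the error reverses the ordering of the arms. The documents do not show this. The incentives are designed to be of equal value, the other cost items are not priced, and payouts rise with adherence and LDL lowering, so cost per mg/dl need not worsen in proportion.

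**Conclusion.** The point holds for the secondary societal analysis. As written, that analysis enters a payment from payer to participant as a cost and gives the participant no credit, so the incremental societal cost of each incentive arm against control is too high by the amount actually paid.

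The bounds of $511, $504 and $507.50 per participant apply only at perfect adherence or with all four targets met, and the sweepstakes components are expected values. Enrolment requires imperfect adherence, and the Abstract cites statin adherence of often about 50% in the year after a heart attack, so average payouts should fall below these bounds. The lower figures above rest on assumed success rates and show the range; they are not forecasts.

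A reader might take the maxima over the design difference and conclude that every arm carries about $50 per mg/dl of spurious cost, or about $100 at a 5 mg/dl difference. The payment rule does not allow that for the Outcome arm. Distortion between arms is possible, but its size and direction cannot be established from the documents.

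The conclusion needs only the accounting identity and the plan's own definition of the societal perspective.

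**What to change.** In the protocol's Cost effectiveness analysis paragraph, apply item (1), the incentive payments, to the payer analysis only. In the societal analysis, either leave the payments out or show them as a payer cost with an equal participant receipt, so that they net to zero. Keep the real resource costs there: administration and platform, device, laboratory tests, drugs, and patient time, travel and side effects.

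This costs one sentence and needs no new data. The payer, employer return-on-investment and LDL analyses do not change.
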